### Mental simulation intervention

Participants randomized to the mental simulation intervention, will be presented with written instructions in the form of a standardized script for the mental simulation exercise (Additional file 1). Participants will be instructed to imagine the steps they will take to reduce their alcohol consumption and the salient outcomes they expect to achieve. The instructions will be adapted from Pham and Taylor’s [31] ‘process’ and ‘outcome’ mental simulation scripts. Participants will be required to follow the instructions on the sheet and perform the metal simulation exercise with their eyes closed. Then they will be asked to write about their experience with the visualization exercise in the space provided on the sheet and to memorize it. Written responses will be content analysed to check for compliance with the task. The exercise is expected to take no longer than 10 minutes. Participants randomized to the control condition will receive written instructions in the form of a standardized script for an irrelevant visualization exercise identical in procedure to the mental simulation exercise (Additional file 1). Instead of visualizing reducing their alcohol consumption, however, participants will be required to imagine a recent visit to the cinema or shopping centre. They will also be asked to write down their experiences on the sheet provided. The purpose of the control task is to maintain an equivalent information load to the participants allocated to the mental simulation condition.

### Self-control training

We will use regular practice on an online version of the Stroop color-naming task which will be delivered on the participant’s smartphone as a means to train and improve self-control resource capacity. As a fall back, in case the participant does not have access to a smartphone or does not own a smartphone, we will give participants the opportunity to conduct their self-control training on their personal computer using their web browser. Participants will be randomly allocated to an intervention group that engages in practice on using a ‘challenging’ version of the Stroop task for the duration of the intervention while participants allocated to the comparison group will engage in regular practice on an ‘easy’ version of the task that is not proposed to have any substantive effect on training self-control. Participants will practice on the task twice per day for the four weeks duration of the intervention. The tasks are similar to those developed for use in a previous study [85]. The challenging version of the task requires participants to respond to a series of word items in which the word meaning and the color of the ink in which it is written are incongruent (e.g., the word “green” written in red ink). The easy version is modified such that the word meaning and ink colour are congruent. There are equal numbers of word items with four possible colors (“red”, “green”, “yellow”, and “blue”) presented in random order. Participants will be given instructions on how to perform the task on a smartphone or personal computer during the initial visit to the laboratory. Participants will be offered the opportunity to use a generic smartphone loaned to them by the experimental team, their own smartphone, or their personal computer to engage in the training tasks. Participants will be given ample opportunity to familiarize themselves with the task and to ask any questions. Participants will be informed that they will be prompted to engage in the task via a text message sent to their smartphone or an email to their regular email address containing a URL link. Upon clicking the URL link, participants will be directed to a website to complete the version of Stroop color-naming task corresponding to the condition to which they will be allocated. Participants will be presented with a series of 238 color-word items presented in seven 34-item blocks on their screen with each item presented for 2000 milliseconds (ms). Participants will use a response panel presented on the smartphone touchscreen or their computer keyboard to identify the colour in which the word is written rather than respond to the word meaning. Participants will have 800 ms to provide a response by choosing the colour-word response options. Response latencies for each item will be logged along with errors. If no response is given, the response will be logged as “unanswered” and the next colour-word item will be presented.

The Stroop task is expected to approximately 5 minutes. Participants will complete the task to which they have been assigned immediately after the mental simulation task in the initial session and then repeat the Stroop task twice per day when prompted, at 7 am and 5 pm, throughout the four-week intervention period. All participants’ Stroop data will be uploaded to, and stored on, a remote computer server for subsequent retrieval to compliance analysis.

Participants will be reminded to practice the Stroop task once per week via emails and/or text messages throughout the four-week intervention period. After four weeks participants will be sent a series of reminder emails to prompt them to complete follow-up dependent measures of self-reported alcohol consumption and follow-up measures of psychological mediator variables, identical to those administered at baseline. Thereafter, participants will receive a full debrief and provided with an opportunity to receive the final group-level results of the intervention.

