### Participants

Participants will be undergraduate students from a large University in Western Australia. Students will be eligible to participate if that are 18 years or older and non-abstinent with respect to alcohol consumption to be eligible to participate in the study. Participants will be excluded if they are heavy or dependent drinkers as identified by the Fast Alcohol Screening Test (FAST) [103]. Participants will be recruited using email circular and notice board advertisements distributed throughout the University and from a dedicated participant pool for undergraduate psychology students incentivised by course credit or a prize draw for shopping vouchers. The study is described as an intervention to reduce alcohol consumption. Assuming a medium effect size for mental simulation interventions on behavior reported by Pham and Taylor [31] (*d* = 0.56) and an effect size of similar magnitude for the effects of self-control resource training reported in Hagger et al.’s [81] meta-analysis (*d* = .62), a power analysis using G*Power v3.1 [104] setting power at .80 and alpha at .05, estimates that we will require a total sample size of between 120 and 144 participants with between 30 and 36 participants in each intervention group. The variation in the sample size estimate is due to the use of the two different effect sizes to compute the power analysis, each of which gives a slightly different result.

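### Eligibility does not require adequate colour vision, although the randomised self-control training depends on telling red, green, yellow and blue ink apart quickly

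*Protocol article*

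**What the plan says.** The Participants section of the protocol article gives the entry rules. The population is described thus: "Participants will be undergraduate students from a large University in Western Australia". The inclusion rule reads: "Students will be eligible to participate if that are 18 years or older and non-abstinent with respect to alcohol consumption". The only stated exclusion is heavy or dependent drinking on the Fast Alcohol Screening Test (FAST). Colour vision is not mentioned there or elsewhere in the article.

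The Self-control training section describes the task. Participants use a response panel "to identify the colour in which the word is written rather than respond to the word meaning", with 800 ms to respond, and items without a response are logged as unanswered. On the colours it says: "There are equal numbers of word items with four possible colors", namely red, green, yellow and blue. In the challenging version "the word meaning and the color of the ink in which it is written are incongruent", and the article's own example is a red/green conflict. For the comparison arm: "The easy version is modified such that the word meaning and ink colour are congruent".

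The Data analysis section uses the resulting Stroop data to examine compliance, to compare compliance between the two versions, and to test weekly mean latencies in a training-by-week ANOVA.

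**The concern.** The task trains inhibition only where the participant can see which ink colour is correct. The stated criteria do not secure that ability, and the two versions differ in how far they need it. In the easy version the word always gives the right answer, so poor colour discrimination can be bypassed by reading. In the challenging version the word is always wrong, so the participant must rely on the ink.

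Randomisation balances the number of affected people between the versions. It does not balance the consequence, because the task version itself creates it. Two things are at stake: a small loss in the contrast between challenging and easy training, and Stroop errors, unanswered items and slow responses that reflect vision rather than self-control and fall mainly in the challenging arm.

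**Working it through.** **Inputs.** From the Participants section: d = 0.56 (mental simulation), d = 0.62 (self-control training), power 0.80, alpha 0.05, total N of 120 to 144 with 30 to 36 per group, hence 60 to 72 per Stroop version. Assumption: a share p of 2% to 8% of participants has impaired colour discrimination. The article gives no figure.

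**Reproducing the plan's sample size.** With f = d/2, noncentrality N × f² and a four-group omnibus F test (3 numerator df), the required N is 144 for d = 0.56 and 118 for d = 0.62. Rounded up to equal groups, 118 becomes 4 × 30 = 120. This matches the stated range.

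**How many people.** 0.02 × 144 = 2.9 and 0.08 × 144 = 11.5, so about 3 to 12 in total. Half of these, 1.4 to 5.8, would be in the challenging arm.

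**How much of the task is affected.** Four inks with three non-matching words each give 12 incongruent pairs. For someone who cannot tell red from green:
- Yellow or blue ink: 6 pairs, conflict intact.
- Red ink with the word green, or green ink with the word red: 2 pairs, resolvable in principle because the ink cannot be the colour named.
- Red or green ink with the word yellow or blue: 4 pairs, truly ambiguous.

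If the pairs are equally frequent (assumption), 4/12, or one third, of the challenging items are ambiguous. In the easy version none is, because the word settles the answer.

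**Dilution, upper bound.** Suppose affected people in the challenging arm get no training effect at all. Then d becomes 0.62 × (1 − p). Main-effect power is P(F′ > F critical) with 1 and N − 6 df (four groups, two covariates) and noncentrality N × (d/2)². For example, at N = 120 the noncentrality is 120 × 0.31² = 11.5 with nobody affected.

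| p | d | Power, N = 120 | Power, N = 144 | Omnibus N for 80% power |
|---|---|---|---|---|
| 0% | 0.620 | 92.0% | 95.9% | 118 |
| 2% | 0.608 | 91.0% | 95.2% | 123 |
| 5% | 0.589 | 89.2% | 93.9% | 130 |
| 8% | 0.570 | 87.2% | 92.5% | 139 |

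**Dilution, milder case.** If affected people lost only the ambiguous third of the training benefit, then at p = 8% d = 0.62 × (1 − 0.08 × 4/12) = 0.603.

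The interaction contrast shrinks by the same factor, since the training effect is reduced alike at both levels of mental simulation.

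**The case against.** The strongest reply is that this is an unlisted criterion in a journal article, and a fuller protocol may contain it. That stands as a caution: if it does, the point falls away. But the article does state its inclusion and exclusion rules, and as stated they admit people for whom the randomised task may not work as designed.

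A second reply is that the laboratory visit would expose gross difficulty: "Participants will be given ample opportunity to familiarize themselves with the task and to ask any questions". This is instruction, not a screen. Anyone practising the congruent version can succeed by reading, so a problem seen during work on the assigned version would show mainly in the challenging arm. Excluding people at that stage would make exclusions depend on arm.

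A reader might also infer more than the article supports:
- *That affected students cannot do the challenging training.* About two thirds of the incongruent pairs remain answerable, the shades are not stated, and mild impairment need not prevent colour naming.
- *That an English-reading criterion is also needed.* These are undergraduates at an Australian university, and every arm requires reading and writing in response to a script. Weak reading would reduce Stroop interference; it would not block the challenging version alone.
- *That vision-driven errors would be counted as feigned compliance, in the challenging arm only.* The Data analysis section ties feigned compliance to meaningless responding and does not say that errors count as such. Error rates can differ between a conflict task and a no-conflict task whatever the colour vision.
- *That the main result is biased towards benefit.* Affected people are spread over both versions, so the expected consequence is dilution. No stated rule removes participants from the primary ANCOVA on compliance.

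**Conclusion.** The point holds as a minor gap in eligibility, limited to colour vision. It slightly weakens the self-control contrast and may add vision-related noise to the Stroop errors and latencies, mainly in the challenging arm. It does not threaten the main result.

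Under an assumed 2% to 8% affected, d falls from 0.62 to between 0.608 and 0.570 even if affected people gain nothing. Main-effect power stays at 87.2% or more at N = 120, and the omnibus sample size rises to at most 139, still within the planned 144. These figures rest on the assumed prevalence, on the article's own d of 0.62, and on a zero training effect in affected people, which is harsher than the count of item pairs suggests.

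**What to change.** Add *self-reported normal colour vision* to the eligibility criteria in the Participants section, and ask about it at screening together with the FAST. The answer must be recorded before allocation, so that no exclusion can depend on the task version received.

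The cost is one screening question and the loss of a few students (about 3 to 12 per 144 screened, under the assumed prevalence). The results would then apply to people with normal colour vision, which should be said when the population is described.

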### Procedure

On recruitment, participants will be required to attend an initial laboratory session with the experimenter at a mutually agreed time. Participants will be provided with an information sheet outlining their expectations and given the opportunity to ask questions about study requirements prior to completing and signing a consent form. They will then be asked to complete a brief demographic questionnaire and baseline self-report measures of alcohol consumption and psychological mediator variables. Next, participants will be given an envelope corresponding to the condition to which they have been allocated that contains instructions for the mental simulation or control manipulations. The envelopes will be prepared by an independent researcher using coded labels to represent the mental simulation manipulation and control irrelevant visualization task so that the experimenter will be blind to the intervention conditions until the end of the study. All participants will be presented with a written script with a generic introduction section providing a brief rationale for changing their alcohol behavior. The instructions will inform participants that the purpose of the study is to keep their alcohol consumption within nationally-recognized ‘safe’ guideline limits to promote better health and reduce adverse effects. A definition of NHMRC guideline limit for alcohol consumption of 14 standard drinks per week, a definition of a standard drink, and examples of volumes and measures of typical drinks that constitute a standard drink will be provided. This will be followed by instructions for the mental simulation or control irrelevant visualization exercise according to the randomly-allocated trial condition (see Additional file 1).

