### Primary and secondary outcome measures

Our primary outcome measure is participants’ self-reported alcohol consumption over the previous four weeks consistent with NHMRC guidelines [4]. Our secondary dependent variable is participants’ self-reported number of binge drinking occasions over the previous four weeks. Both primary and secondary outcome measures will administered at baseline and at follow-up. Participants will be asked to recall and report the absolute number of standard drinks they had consumed and the number of occasions when they engaged in binge drinking, that is, exceeding more than 4 standard drinks on a single drinking occasion, per week over the previous four weeks [34,105]. The self-report measures are based on the time-line follow back technique which has been shown to provide precise estimates of alcohol drinking [106]. This measure uses a number of techniques to aid recall such as linking alcohol drinking with significant events. In addition, the FAST will be administered to students recruited to the study at baseline [103]. The measure comprises four items (e.g. “How often during the last year have you failed to do what was normally expected of you because of drinking?”) and has demonstrated adequate validity and reliability to assess the extent of heavy and dependent drinking. FAST scores will be used as a means to screen participants for heavy alcohol consumption that is indicative of alcohol dependency. Participants identified as heavy or dependent drinkers will be excluded from the study prior to engaging in the protocol. Participants identified as heavy or dependent drinkers by the FAST will be provided with a leaflet providing advice on how to seek professional help for their alcohol consumption.

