### Measures of psychological mediator variables

In keeping with research examining the effects of the intervention components on behavior, we will include measures of key psychological variables that are likely to mediate the impact of the motivational and self-control intervention techniques on alcohol consumption. Mental simulations are likely to be mediated by social cognitive variables related to motivation. In keeping with previous research that has demonstrated significant effects of mental simulations on variables form the theory of planned behavior, we will measure participants’ intentions, attitudes, perceived behavioral control, and subjective norms toward alcohol consumption. Standardized measures of the theory of planned behavior constructs used in previous studies will be adopted [42,107]. Intentions will be assessed with three items (e.g. “I intend to keep my alcohol drinking to within safe limits on each individual occasion or session over the next four weeks”) rated on six-point Likert-type scales ranging from 1 (*extremely unlikely*) to 6 (*extremely likely*). Attitudes will be assessed using five semantic-differential items (e.g. *enjoyable-unenjoyable*, *important-unimportant*) on six-point scales in response to a common stem (“For me, keeping my alcohol drinking to within safe limits on each individual occasion or session over the next four weeks is…”). Perceived behavioral control will be measured using three items (e.g. “How confident are you that you can keep your alcohol drinking to within safe limits on each individual occasion or session over the next four weeks?”) on six-point Likert-type scales ranging from 1 (*no control at all*) to 6 (*complete control*). Subjective norms will be assessed using three items (e.g. “Most people I know would approve of me keeping my alcohol drinking to within safe limits on each individual occasion or session over the next four weeks.”) on six-point Likert-type scales ranging from 1 (*disagree*) to 6 (*agree*). We will also assess generalized motivation to reduce alcohol consumption based on measures identified in previous research [34,107,108]. The motivation measure will adopt three items (e.g. “How motivated are you to keep your alcohol drinking to within safe limits on each individual occasion or session over the next four weeks?”) with responses made on six-point Likert-type scales ranging from 1 (*not at all motivated*) to 6 (*extremely motivated*).

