We will also conduct mediation analyses to evaluate the effectiveness of the intervention components on alcohol consumption. This will be conducted using moderated linear regression analyses with indirect effects reproduced using Preacher, Curran, and Bauer’s [110] asymptotic bootstrapped algorithms and the bias-corrected bootstrap confidence interval to assess the statistical significance of the effects [111]. Specifically, we will develop binary dummy-coded variables to represent the effects of the mental simulation (1 = received mental simulation, 0 = received irrelevant visualization strategy) and self-control training (1 = received challenging Stroop task, 0 = received easy Stroop task) interventions with an additional variable computed to represent the interaction of the two. The primary outcome variable, follow-up alcohol consumption, will be regressed on these coded variables in the first instance to ascertain direct effects. This will be followed by analyses including multiple mediators of the effects including residualized change scores for the baseline and follow-up measures of the theory of planned behavior variables (intentions, subjective norms, attitudes, perceived behavioral control) and motivation as mediators of the mental simulation intervention and residualized change scores in state perceived self-control between baseline and follow-up as a mediator of the effect of the self-control training intervention. The unstandardized effects and confidence intervals will be used as input for Preacher et al.’s [110] bootstrapped algorithm computational tool to compute the indirect effects. We predict statistically-significant, medium-sized multiple mediation of the effects of the mental simulation intervention on follow-up alcohol consumption by the theory of planned behavior and motivational change scores and significant mediation of the effect of self-control training on alcohol consumption by state self-control change scores. Trait self-control will be included in the analyses as a control variable.

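### Mediators are re-measured only at week 4, after the drinking they are meant to explain, so the planned mediation analysis cannot separate mediation from reverse causation

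*Protocol article*

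**What the plan says.** All references are to the protocol article.

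- **Procedure.** At the laboratory visit participants complete "baseline self-report measures of alcohol consumption and psychological mediator variables". The manipulation comes after this: "Next, participants will be given an envelope corresponding to the condition to which they have been allocated".
- **Self-control training (last paragraph).** After four weeks participants complete the drinking measures and "follow-up measures of psychological mediator variables, identical to those administered at baseline". No other administration of the mediators is described.
- **Primary and secondary outcome measures.** The primary outcome is "self-reported alcohol consumption over the previous four weeks consistent with NHMRC guidelines". Participants report drinks and binge occasions week by week within that window.
- **Measures of psychological mediator variables.** The example intention item reads "I intend to keep my alcohol drinking to within safe limits on each individual occasion or session over the next four weeks". The examples for attitude, perceived control, norms and motivation carry the same forward-looking period. The state self-control scale asks about present capacity.
- **Data analysis.** Follow-up drinking is regressed on the condition codes and then on mediators. These are "residualized change scores for the baseline and follow-up measures of the theory of planned behavior variables", the corresponding change in motivation and, for the training component, the change in state self-control. Significant mediation is predicted.
- **Discussion and Implications.** The mediation results are presented as helping to identify mechanisms, as causal knowledge beyond what correlational designs give, and as showing which mediators carry the effects.

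**The concern.** A mediation claim needs the mediator to change after the manipulation and before the outcome. Here the only post-manipulation score is taken when the outcome window has closed. A student who drank less for any reason may then report firmer intentions, more confidence or more self-control because of it. In the planned regression this produces the same pattern as mediation: condition predicts the mediator change, and the mediator change predicts drinking given condition. Randomization protects the path from condition to mediator but not the path from mediator to drinking.

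The opposite error is also possible. The mental simulation is a single exercise of at most ten minutes. A short-lived gain in motivation directly after it would not be recorded.

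At stake is the explanatory aim, which the article uses to set this trial apart from earlier interventions. No later analysis can supply a measurement that was not taken.

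**Working it through.** **1. Time line.**

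| Quantity | Recorded | Refers to |
|---|---|---|
| Mediators, first time | week 0, before the envelope | planned behavior and motivation: weeks 0-4; state self-control: now |
| Drinking outcome | week 4 | weeks 0-4 |
| Mediators, second time | week 4 | planned behavior and motivation: weeks 4-8; state self-control: now |

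The residualized change is complete only at week 4. Residualizing on the baseline score removes baseline differences but does not move the second measurement earlier.

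**2. The plan's own figure.** The article gives no figure for the mediation analysis. Its only design figure is a "total sample size of between 120 and 144 participants with between 30 and 36 participants in each intervention group", from d = 0.56 and d = 0.62, "setting power at .80 and alpha at .05". This reproduces with a four-group F test on 3 numerator df, f = d/2 and noncentrality N·f²:
- d = 0.56: f = 0.28, N = 144 (144 × 0.0784 = 11.29).
- d = 0.62: f = 0.31, N = 118 (118 × 0.0961 = 11.34), or 120 when rounded up to a multiple of four.

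These values of N are used below.

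**3. Model with no mediation.** The mediator has no effect on drinking and only responds to it:
- Y1 = 0.5·Y0 − 0.56·X + √0.75·e (within-arm SD 1, so the direct effect is the article's d = 0.56)
- M0 = −0.3·Y0 + v
- M1 = 0.5·M0 − k·Y1 + √0.75·u

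X is mental simulation, and e, u and v have variance 1. Every coefficient except 0.56 is an assumption, including the reverse path k. R is M1 residualized on M0. Drinking is regressed on both conditions, baseline drinking and R.

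**4. Expected false indirect effect in large samples.**
- Path a (X to R) = 0.56·k.
- Path b (R to Y1) = −0.75·k / [0.75 + k²·(0.75 + c²)], with c = 0.15/1.09 = 0.138, so the bracket is 0.75 + 0.769·k².
- False mediated share = a·b / (−0.56) = 0.75·k² / (0.75 + 0.769·k²).

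This gives 0.030/0.781 = 3.8% at k = 0.2, 0.0675/0.819 = 8.2% at k = 0.3, and 0.1875/0.942 = 19.9% at k = 0.5. The true share is zero.

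**5. How often mediation is declared.** Bias-corrected bootstrap, one mediator, 200 trials per setting with 200 resamples each:

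| k | N = 120 | N = 144 | Simulated false share |
|---|---|---|---|
| 0 | 1.5% | 1.0% | about 0 |
| 0.2 | 12% | 13% | about 4% |
| 0.3 | 18.5% | 18.5% | about 7% |
| 0.5 | 42% | 44% | about 20% |

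The simulation standard error is √(0.185 × 0.815/200) = 2.7 points at 18.5% and √(0.44 × 0.56/200) = 3.5 points at 44%. The shares agree with step 4 within simulation error.

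**6. Sensitivity, using a Monte Carlo interval for a·b.**
- One mediator, 3,000 trials, slightly different coefficients, k = 0.3/0.4/0.5: 24/36/48% at N = 144 and 20/31/41% at N = 120. With baseline drinking as covariate: 23-50% at N = 144.
- One mediator, 2,000 trials, same k: 21/33/42% at N = 144 (20/34/47% with baseline drinking as covariate) and 17/28/36% at N = 120. At k = 0.2: 5-10%. At k = 0: under 0.5%.
- Five mediators together, correlated 0.5 (assumed): at k = 0.3, 1-1.5% for a given mediator and 7-11% for any of the five; at k = 0.5, 9-13% and 39-52%.
- True effect 0.3 instead of 0.56, one mediator, k = 0.3: 7-9%.

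Adjusting for baseline drinking does not remove the problem. The rate depends mainly on k, on the size of the true effect, and on whether mediators are tested singly or together. All runs simplify the planned model: trait self-control is left out, and the table in step 5 also omits the product of the two conditions.

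**The case against.** **Item wording.** A reader might infer that every mediator refers to the wrong period. The documents do not support that. State self-control is the only mediator for the training component, and its scale asks about current capacity. For it, only the timing objection holds.

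**Strength of the claim.** A reader might also infer that these variables cannot mediate, or that reverse causation will be taken for mediation. Both go too far. Training is spread over four weeks of twice-daily practice, and an end-of-period change may be a fair proxy for capacity gained on the way. An earlier change in motivation may have been causal; the design simply does not observe it. What stands is that mediation cannot be shown from these data.

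**Data within the period.** Stroop latencies are logged throughout and analysed by week, so the training component has a process measure inside the outcome window. It is not entered in the mediation model and does not cure the problem.

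**Size.** The reverse path comes from no document. With five correlated mediators or a smaller true effect the false rate can be near or below 5%. This stands: the high rates are the upper part of a wide range.

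**Importance.** The main and interactive effects are tested by ANCOVA on randomized conditions and are not touched. This also stands. It limits the defect to the mediation analysis but does not rescue the mechanistic conclusions drawn from it.

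**Conclusion.** The point holds for the mediation analysis only. The single post-manipulation mediator score follows the whole outcome window. Carrying out the plan exactly as written can therefore declare mediation where drinking changed the mediator, and nothing in the data would reveal it. With no true mediation and assumed reverse paths of 0.2 to 0.5, the false-positive rate runs from around or below the nominal 5% to about 45%, and slightly higher in some runs. The false mediated share is about 4% to 20% in the single-mediator model. These figures rest on assumed reverse paths and simplified models; the timing fault rests on the article's own schedule. The documents do not support reading this as a flaw in the primary ANCOVA, or as proof that the variables play no causal part. The mechanistic claims in Data analysis, Discussion and Implications do go further than the planned data can support.

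**What to change.** 1. **Planned behavior and motivation.** Repeat the 17 items (3 intention, 5 attitude, 3 perceived control, 3 norms, 3 motivation) in the same laboratory session, straight after the simulation or control sheet. Use these scores, adjusted for baseline mediator values and baseline drinking, as mediators of four-week drinking.
2. **State self-control.** Send the 25-item scale once mid-period, at the end of week 2, through the existing online link. For this mediation model only, use drinking in weeks 3-4 as the outcome; weekly counts are already requested. The primary outcome stays as it is.
3. **Week-4 mediator changes.** Report them as associations, and limit the mechanistic statements in Data analysis, Discussion and Implications to match.
4. **If no measure can be added,** relabel the planned mediation analysis as associational.

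**Cost.** A few extra minutes in a visit already attended, one online questionnaire, and item repetition. Answering the same items minutes after an alcohol-reduction script may invite demand or consistency responding that differs by arm, and this should be stated as a limitation. The mid-period scale is one more prompt in every arm, and the self-control model uses only half of the outcome period.

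**What remains.** The change restores time order but does not randomize the mediator. Drinking in weeks 1-2 may still influence the week-2 score and predict weeks 3-4, so causal wording should stay cautious.
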